# Rationale and study design of an early care, therapeutic education, and psychological intervention program for the management of post-intensive care syndrome and chronic pain after COVID-19 infection (PAIN-COVID): study protocol for a randomized controlled trial

**DOI:** 10.1186/s13063-021-05463-7

**Published:** 2021-07-24

**Keywords:** COVID-19, Randomized controlled trial, Protocol, Post ICU syndrome, Chronic pain, Critical illness

## Abstract

**Background:**

Critically ill patients with COVID-19 are an especially susceptible population to develop post-intensive care syndrome (PICS) due to acute respiratory distress syndrome (ARDS). Patients can suffer acute severe pain and may have long-term mental, cognitive, and functional health deterioration after discharge. However, few controlled trials are evaluating interventions for the prevention and treatment of PICS. The study hypothesis is that a specific care program based on early therapeutic education and psychological intervention improves the quality of life of patients at risk of developing PICS and chronic pain after COVID-19. The primary objective is to determine whether the program is superior to standard-of-care on health-related quality of life at 6 months after hospital discharge. The secondary objectives are to determine whether the intervention is superior to standard-of-care on health-related quality of life, incidence of chronic pain and degree of functional limitation, incidence of anxiety, depression, and post-traumatic stress syndrome at 3 and 6 months after hospital discharge.

**Methods:**

The PAINCOVID trial is a unicentric randomized, controlled, patient-blinded superiority trial with two parallel groups. The primary endpoint is the health-related quality of life at 6 months after hospital discharge, and randomization will be performed with a 1:1 allocation ratio. This paper details the methodology and statistical analysis plan of the trial and was submitted before outcome data were available.

The estimated sample size is 84 patients, 42 for each arm. Assuming a lost to follow-up rate of 20%, a sample size of 102 patients is necessary (51 for each arm).

**Discussion:**

This is the first randomized clinical trial assessing the effectiveness of an early care therapeutic education, and psychological intervention program for the management of PICS and chronic pain after COVID-19. The intervention will serve as proof of the need to implement early care programs at an early stage, having an incalculable impact given the current scenario of the pandemic.

**Trial registration:**

This study is being conducted in accordance with the tenets of the Helsinki Declaration and has been approved by the authors’ institutional review board *Comité Ético de Investigación Clínica del Hospital Clínic de Barcelona* (approval number: HCB/2020/0549) and was registered on May 9, 2020, at clinicaltrials.gov (NCT04394169).

**Supplementary Information:**

The online version contains supplementary material available at 10.1186/s13063-021-05463-7.

## Introduction

Since the initial outbreak of COVID-19 in December 2019, there have been more than 14.3 million cases of infection with the SARS-CoV-2 virus reported worldwide [1]. This has led to a large number of hospital admissions testing the capability of many healthcare systems. Among hospitalized patients, 10–20% are admitted to the intensive care unit (ICU), and more than 70% of those require invasive mechanical ventilation with an overall mortality over 30% [2–4].

Critical care survival has been reported as 16–37%, and this will result in an unimaginable size of a cohort of critical care survivors given the number of global infections; these patients can experience a significant worsening of their health status and deterioration of their quality of life [5]. In 2012, the Society of Critical Care defined a new term, the post-intensive care syndrome (PICS), as the worsening of the physical, mental or cognitive patient’s status after a critical illness that is maintained beyond hospitalization. Consequently, health-related quality of life (HRQoL) and post-intensive care syndrome (PICS) is becoming the focus of intensive care medicine rather than survival rate alone [6, 7]. As psychological dysfunction can persist for years after ICU discharge, its management is becoming an important strategy to improve quality of life together with early detection of posttraumatic stress disorder and anxiety and depression [8]. Moreover, there is evidence that patients who survive a critical illness have a high prevalence of moderate to extreme chronic pain being an essential factor affecting their ability to return to work and to restore quality of life for up to 5 years following discharge [9]. However, few controlled trials have evaluated interventions for the prevention and treatment of PICS [10].

Patients with COVID-19 are an especially susceptible population to develop PICS due to acute respiratory distress syndrome (ARDS). Patients can suffer acute severe pain and may have long-term deterioration in their mental, cognitive, and functional health after discharge. However, pain is a conscious experience by definition; thus, sedated patients can suffer a high nociceptive input inadvertently [5]. However, there are recent publications describing nervous system involvement after infection with SARS-CoV-2 [11, 12]. Thus, chronic pain could potentially occur as a complication or sequel of COVID-19. However, as far as we know, there are no studies related to chronic pain care after a critical illness, specifically in patients with COVID-19 [13].

We hypothesize that a specific care program based on early therapeutic education and a psychological intervention improves the quality of life of patients at risk of developing PICS and chronic pain after COVID-19.

### Primary outcome

The primary objective is to determine if a specific care program based on early therapeutic education and a psychological intervention improves the health-related quality of life (HRQoL) compared to standard care at 6 months after hospital discharge.

### Secondary outcomes

The secondary objectives are to determine if the intervention is superior to standard-of-care, by evaluating:
The HRQoL at three months after hospital discharge.The incidence of chronic pain and the degree of functional limitation at 3 and 6 months after hospital discharge.The incidence of anxiety and depression at 3 and 6 months after hospital discharge.The incidence of post-traumatic stress syndrome at 3 and 6 months after hospital discharge.

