#### General procedures

The study subjects will be assigned to one of two arms, and the intervention program will be compared to the standard-of-care clinical practice. The baseline visit will take place 4 to 6 weeks after hospital discharge, and two follow-up visits will take place 3 and 6 months after.

The intervention program will consist of an early care therapeutic education on prevention and management of PICS and chronic pain during the three scheduled medical visits within the first 6 months after hospital discharge and psychological treatment for patients at risk of emotional distress.

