#### Baseline visit

The baseline visit will take place between 4 to 6 weeks after hospital discharge. Information regarding the study will be given to the patient, and informed consent will be obtained. After that, the patient will be randomized. During this first visit, demographic data, medical history, and ICU and hospitalization variables will be collected from all the included patients, regardless of their randomization arm. All patients will complete a series of questionnaires to evaluate their quality of life and the presence of anxiety, depression, or post-traumatic stress disorder. The presence of pain and its influence on the patients’ lifes will also be evaluated.

Intervention group

The intervention consists of a program that includes early patient care, therapeutic education, and psychological intervention. It will be implemented across three medical visits scheduled as follows:
Visit 1 Intervention group, 4 to 6 weeks after hospital discharge.Visit 2 Intervention group, 8 weeks after hospital discharge.Visit 3 Intervention group, 18 weeks after hospital discharge.

Components:
Interview and physical examination.Therapeutic education about the PICS, orally and in writing with specific documents delivered at the end of the visit, i.e., a PICS fact-sheet developed by the investigators and a rehabilitation manual recommended by the Follow-up and Rehabilitation Committee of the Argentine Society of Intensive Care, SATI [14].Therapeutic education about pain (if the patient reports pain) which includes an explanation of pain neurophysiology, the rational use of drugs prescribed by other specialists, information about how to manage daily life activities, and the importance of pre-emptive pain management for proper rehabilitation.

A psychological intervention will be conducted if the following criterium is met: a score higher than 8 on the hospital anxiety and depression (HAD) test depression subscale (supplement, questionnaire Q1) [17]. The intervention protocol will consist of 7 weekly sessions lasting one and a half hours each (supplement, Table 1). The intervention in depression is based on Rehm’s model of self-control. Psychological interventions may cause adverse events resulting in worsening of patients’ clinical course (overdose, self-harm, and self-harm attempts). Therefore, the investigators will monitor any related symptom, report it as an adverse event, and refer the patient for treatment by a specialist unit.

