The impact of the intervention program on the incidence of anxiety or depression will be assessed by the Hospital Anxiety and Depression test (HAD) (supplement, questionnaire Q1) [17], consisting of 14 questions, with two subscales, one for anxiety and the other for depression, with seven items each and a maximum score of 21 for each subscale. The cut-off points are as follows: 0 to 7 imply the absence of clinically relevant anxiety and depression, 8 to 10 imply de presence of symptoms that require consideration, and 11 to 21 it report the presence of relevant symptoms, with a very probable diagnosis of anxiety or depression. According to Bjelland’s review, cut-off points equal or greater that 8 will be used as abnormal anxiety or depression’s values. This test will be performed at the baseline visit and at 3 and 6 months [25].

Finally, the incidence of post-traumatic stress disorder (PTSD) [26] will be evaluated with the post-traumatic stress disorder checklist questionnaire (PCL-5) [27]. It contains 20 questions that correspond to the DSM-V criteria. Participants will rate their symptoms on a scale of 0 (not at all), 1 (slightly), 2 (moderately), 3 (quite) to 4 (extremely), with a score ranging from 0 to 80. The overall severity of the symptoms can be assessed adding up the scores of each question (interval 0–80). The severity of each symptom can also be evaluated adding up the scores of the questions. DSM-5 symptom cluster severity scores can be obtained by adding up the scores for the items within a given cluster, i.e., cluster B (items 1–5), cluster C (items 6–7), cluster D (items 8–14), and cluster E (items 15–20). A provisional PTSD diagnosis can be made by treating each item rated 2 (“moderately”) or higher as a symptom endorsed, then following the DSM-5 diagnostic rule which requires at least: 1 B item (questions 1–5), 1 C item (questions 6–7), 2 D items (questions 8–14), and 2 E items (questions 15–20) (supplement, questionnaire Q6).

For this analysis, questionnaire licensing was obtained. The validated version in Spanish was used for each of them, except for PCL-5 which, being a new questionnaire, is not yet validated in Spanish, but it has the advantage of screening PTSD according to the DSM-V criteria. The questionnaires are shown in the supplement.

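### Depression is named as an incidence outcome, yet every patient who qualifies for the psychological component is already a case by the outcome's own cut-off

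*Protocol article*

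**What the plan says.** Four statements in the protocol article bear on this point.

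- **Objective (Secondary outcomes).** "The secondary objectives are to determine if the intervention is superior to standard-of-care, by evaluating", among other items, "The incidence of anxiety and depression at 3 and 6 months after hospital discharge". Post-traumatic stress is also listed as an incidence at the same two times.
- **Who receives the psychological component (Baseline visit, Intervention group).** The condition is "a score higher than 8 on the hospital anxiety and depression (HAD) test depression subscale". The anxiety subscale plays no part. General procedures describes the recipients differently, as "psychological treatment for patients at risk of emotional distress".
- **Case definition and timing (Outcome measurements).** "The impact of the intervention program on the incidence of anxiety or depression will be assessed by the Hospital Anxiety and Depression test (HAD"), with "cut-off points equal or greater that 8 will be used as abnormal anxiety or depression’s values". On timing: "This test will be performed at the baseline visit and at 3 and 6 months".
- **Analysis (Data analysis).** Categorical variables are compared between groups by chi-square or exact tests, under intention-to-treat.

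Depression at baseline is not among the exclusion criteria (Study population). No section defines an at-risk set or removes baseline cases.

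**The concern.** Incidence ordinarily means new cases among people free of the condition at the start. Here the component aimed at depression goes to people who already have it by the trial's own definition. The objective's name and the treatment rule therefore point at different patients, and the article does not say which are to be counted.

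The choice changes the analysis. An analyst who takes the word literally would remove baseline cases, and with them every patient given therapy on the baseline HAD. An analyst who tests status at the visit keeps them, but then reports a mixture of persistence and new onset under a name that belongs only to new onset. The Discussion says that the study would quantify the incidence of anxiety, depression and PTSD, so the label would carry through to the published results.

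**Working it through.** The article gives no figure for the depression outcome, so there is none to reproduce. The check first compares the two cut-offs, then illustrates the two readings.

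**Step 1. Trigger against case definition.** Each HAD subscale runs to 21 (Outcome measurements).

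- Trigger for therapy: depression score above 8, that is 9 to 21.
- Depression case: score of 8 or more, that is 8 to 21.

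The first range lies wholly inside the second. The share of patients treated on the baseline HAD who could later count as a new depression case is therefore 0%. A score of exactly 8 makes a patient a case who does not qualify for therapy.

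**Step 2. Anxiety and post-traumatic stress.** The trigger uses the depression subscale alone. A recipient may be below the anxiety cut-off and the PCL-5 criterion at baseline and so remain at risk of both, so Step 1 does not carry over. What does carry over is the label: all three conditions are assessed at baseline (Baseline visit), no baseline cases are removed, and status at the visit again mixes persistence with new onset.

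**Step 3. The two readings in numbers.** All rates are assumptions, since the article states none.

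- b = proportion who are cases at baseline: 20%, 30%, 40%.
- New onset among baseline non-cases: 10% in both arms, so the true difference in incidence is zero.
- Remission among baseline cases: 40% control, 70% intervention.
- Evaluable patients per arm: 42 (Sample size).

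Status at the visit = b × (1 − remission) + (1 − b) × 0.10

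| b | Control | Intervention | Difference | At-risk set per 42 | Baseline cases per 42 |
|---|---|---|---|---|---|
| 20% | 0.20×0.60 + 0.80×0.10 = 20% | 0.20×0.30 + 0.80×0.10 = 14% | 6 points | 33.6 | 8.4 |
| 30% | 0.30×0.60 + 0.70×0.10 = 25% | 0.30×0.30 + 0.70×0.10 = 16% | 9 points | 29.4 | 12.6 |
| 40% | 0.40×0.60 + 0.60×0.10 = 30% | 0.40×0.30 + 0.60×0.10 = 18% | 12 points | 25.2 | 16.8 |

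With equal new onset, the difference is simply b × (gap in remission). At b = 15% and 45% with the same 30-point gap it is 4.5 and 13.5 points. With a 50-point gap (persistence of 70% against 20%) and b = 15%, 30% or 45%, it is 7.5, 15 or 22.5 points. In every row a strict new-case endpoint shows a difference of zero, and the visit-status endpoint shows a difference that comes entirely from remission.

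The illustration applies the intervention-arm remission rate to all baseline cases, including the few who score exactly 8.

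**The case against.** The strongest reply is that the article means status at the visit. It applies one cut-off at baseline, 3 and 6 months, excludes no one for baseline depression, names no at-risk set, and plans an intention-to-treat comparison of proportions. On that reading, comparing the proportion at or above 8 between randomised arms is a valid test, and a lower proportion is a real benefit whether it comes from remission or from fewer new cases. This stands. The illustration shows it too: visit status does pick up the remission effect. What remains on this reading is a wrong name for the quantity.

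Three further points are fair. The objective tests the whole programme, and education on post-intensive care syndrome goes to the whole intervention arm, so even a strict new-case endpoint would test something. The sentence giving the trigger names no visit; baseline is inferred from the heading above it, and the HAD is repeated. This is why the 0% is limited to patients treated on the baseline HAD. And the rates in the illustration have no source in the article.

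It can also be said that definitions belong in an analysis plan. But the article's abstract says that it details the statistical analysis plan, and the problem is a stated term that does not fit the stated trigger and cut-off. Listing separate remission and new-onset tables would, by contrast, be ordinary plan detail, and their absence alone is no fault.

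**Conclusion.** The mismatch is real, and it is narrower than it first looks. On a strict new-case reading, the depression endpoint excludes every patient treated on the baseline HAD and cannot register therapy's effect on them. On the visit-status reading, which the article's analysis section favours, the test is sound but the quantity is prevalence. For anxiety and post-traumatic stress only the second point applies. The step from trigger to case status rests on the article's own cut-offs; the 6 to 12 points rest wholly on assumed rates and show direction, not an expected size.

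A reader might infer more than this, and the documents do not support it:

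- *That the objective cannot show the psychological component's effect at all, or that the conclusion is wrong on either reading.* Both fail under visit status in all randomised patients.
- *That the result will be reported as prevention of depression.* The article speaks of prevention and management of post-intensive care syndrome and chronic pain; it never promises a claim about preventing depression.
- *That the trial's main psychological question is whether therapy reduces existing depression.* The stated question is whether the programme is superior to standard care.

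The primary outcome is untouched. The correction is worth making because it is cheap and rules out an analysis that would discard the treated patients.

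**What to change.** 1. Define the anxiety, depression and post-traumatic stress outcomes as the proportion meeting the HAD cut-off or PCL-5 criterion at 3 and at 6 months in all randomised patients, and call this prevalence.
2. Replace the unadjusted chi-square comparison for these outcomes with one adjusted for baseline case status, or compare the continuous HAD and PCL-5 scores adjusted for their baseline values. The baseline measurements are already collected, and adjustment should add precision.
3. Report, by arm and descriptively, remission among baseline cases and new onset among baseline non-cases. Keep the word incidence for new onset.
4. Reconcile the passages on who receives the psychological component: General procedures refers to risk of emotional distress, Baseline visit to a score above 8, and Outcome measurements to 8 or more as abnormal. The visit whose score counts should be stated. Which rule applies is for the investigators to settle.

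The cost is a change of wording, a changed model for these secondary outcomes, and one extra table. No new data are needed. The downside is that the strata in that table are small: under the assumed 20 to 40% baseline prevalence, about 8 to 17 baseline cases per arm of 42, so the estimates will be imprecise and should not be tested formally.

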## Methods

### Study design

The PAIN-COVID is a comparative, prospective, single-center randomized controlled trial that will include 102 patients (Fig. 1). The trial has been designed in accordance with the fundamental principles established in the Declaration of Helsinki, the Convention of the European Council relating to human rights and biomedicine, and the Universal Declaration of UNESCO on the human genome and human rights, and with the requirements established by Spanish legislation in the field of biomedical research, the protection of personal data, and bioethics, registered on May 9, 2020, at http://www.clinicaltrials.gov with identification No. (NCT04394169). Approval of the final protocol by the *Comité Ético de Investigación Clínica del Hospital Clínic de Barcelona*—approval number: HCB/2020/0549, Chairperson: [name] [name], on May 14, 2020.

**Fig. 1 Fig1:**
[figure not shown]
Summary of patient flow diagram

This study followed the “Standard Protocol Items: Recommendations for Interventional Trials.” The SPIRIT 2013 Statement provides evidence-based recommendations for the minimum content of a clinical trials protocol (Fig. 2).

**Fig. 2 Fig2:**
[figure not shown]
Schedule of enrolment interventions and assessment, SPIRIT 2013

### Study population

Adult patients will be enrolled if they fulfil at least one of the following Inclusion criteria: (1) had SARS-CoV-2 infection, confirmed with a respiratory tract sample using PCR-based tests, (2) had an Acute Physiology And Chronic Health Evaluation (APACHE II) score over 14, (3) ICU stay over 10 days, (4) acquired weakness in ICU [14] (Supplement, Definition D1), (5) delirium during ICU [14] (Supplement Definition, D2), and 6) acceptance to participate in the study by signing the informed consent form.

The exclusion criteria are as follows: (1) patients with non-confirmed SARS-CoV-2 infection according to WHO guidance [15], (2) central ervous system degenerative diseases or terminal illness (Supplement, Definition D3), (3) terminal illness (Supplement, Definition D4) [16], (4) insufficient understanding of the Spanish language, (5) patients with whom it would be difficult to complete follow-up, and (6) not willing to sign the informed consent form.

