### Methods of randomization and bias minimization

Once the informed consent has been obtained, the patient will be assigned 1:1 by the investigator to either the control or intervention group according to the allocation sequence generated by the randomization program. Only the researchers who signed the informed consent had access to this list which was concealed from the principal investigator.

The data for the screening will be obtained from the clinical records program of the Hospital Clínic de Barcelona, where the data of patients who required admission to the ICU, as well as days of admission, will be reviewed by the members of the research team in order to verify whether they are eligible or not.

Screening for patients will be done monthly. Enrolment is expected to be completed within 3 to 6 months. The baseline visit will take place between 4 to 6 weeks after hospital discharge. Follow-up visits will take place at 3 and 6 months after discharge (Fig. 2.)

Patients will be encouraged to remain in the study during each interview by giving them feedback about the importance of their collaboration. Participants who decide to drop out during follow-up will be asked about the reason for it, and all their answers will be recorded.

The database will be paper-based and electronic data entry will also be used using FileMaker. Only three research team members will obtain access to this program. case report forms (CRF) will be kept in the hospital files and all data will be available on the web after study finalization.

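### As worded, the inclusion rule makes the four ICU-severity criteria inoperative, so ICU survivors of COVID-19 with none of those markers are eligible

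*Protocol article*

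**What the plan says.** The Study population section of the protocol article opens: "Adult patients will be enrolled if they fulfil at least one of the following Inclusion criteria: (1) had SARS-CoV-2 infection". The list continues with APACHE II ("score over 14, (3) ICU stay over 10 days, (4) acquired weakness in ICU"), then delirium, and closes with consent: "and 6) acceptance to participate in the study by signing the informed consent form".

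The exclusion criteria in the same section include "patients with non-confirmed SARS-CoV-2 infection according to WHO guidance" and "not willing to sign the informed consent form".

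The section Methods of randomization and bias minimization describes screening from the hospital's clinical records, "where the data of patients who required admission to the ICU, as well as days of admission, will be reviewed" by the research team, and gives the purpose as deciding whether each patient is eligible.

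The Introduction sets the hypothesis: the programme "improves the quality of life of patients at risk of developing PICS and chronic pain after COVID-19".

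**The concern.** A rule that asks for any one of six conditions is only as strict as its easiest condition. Here two of the six, infection and consent, are things every participant must have anyway. The four conditions that describe a severe ICU course then have no work to do.

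The population of the trial's question is at stake. The hypothesis concerns people at risk of post-intensive care syndrome (PICS) and chronic pain, and the four severity criteria look like the means of selecting them. If they do not operate, a patient with a short ICU stay, a low APACHE II score, no weakness and no delirium is eligible. A reader cannot tell whom the result applies to. If such patients have less room to benefit, the average difference between arms shrinks.

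**Working it through.** **Logic check.** Inputs, all from Study population: the six inclusion criteria, the words requiring at least one of them, and exclusions (1) and (6).

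1. Each criterion is met or not met, which gives 2^6 = 64 profiles.
2. At least one met: 64 − 1 = 63 profiles.
3. Exclusion (1) requires confirmed infection and exclusion (6) requires consent. Fixing criteria (1) and (6) as met leaves 2^4 = 16 profiles, one for each combination of criteria (2) to (5).
4. Deleting criteria (2) to (5) from the list leaves the same 16 profiles eligible. The four criteria therefore never alter a decision.

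Consent alone is enough for this result. It does not depend on whether confirmation under WHO guidance (exclusion 1) and confirmation by PCR on a respiratory sample (criterion 1) coincide exactly.

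**The possible readings compared.**

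| Reading | Eligible profiles |
|---|---|
| As written, with exclusions | 16 |
| Infection and consent and at least one of (2) to (5) | 15 |
| All six required | 1 |

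The one profile that separates the first two readings is the infected, consenting patient with none of the four markers. These are counts of profiles, not of patients. The document gives no frequency for any profile.

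**Comparison with the screening text.** Methods of randomization and bias minimization has days of admission reviewed to decide eligibility. Under the rule as written, length of stay has no bearing on eligibility. The two sections do not agree.

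**Illustration of dilution.** From Sample size: control mean 50 on the EQ-5D-5L visual analog scale and a 20% difference, read as 0.20 × 50 = 10 points; one tail, type I error 0.05, power 80%, 42 per arm. No SD is stated, so it has to be solved for:

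SD = 10 × √(42/2) / (1.645 + 0.842) ≈ 18.4 by the normal approximation, or about 18.3 with the t distribution.

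This SD reproduces the plan's 42 per arm by construction, so it is an assumption and no check on that figure. Suppose further that a share q of enrolled patients gets no benefit. The expected difference is 10 × (1 − q), and

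power = Φ( 10(1 − q) / (SD × √(2/42)) − 1.645 ), with SD × √(2/42) = 18.43 × 0.2182 = 4.02.

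| q | Difference (points) | One-sided power, 42 per arm |
|---|---|---|
| 0% | 10 | 80% |
| 10% | 9 | 72% |
| 20% | 8 | 63% |
| 30% | 7 | 54% |

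The t-based calculation with SD 18.28 gives the same percentages. The value of q has no source in the document.

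**The case against.** The strongest reply is that this is garbled drafting and not a failure of the population. Screening starts from patients who required ICU admission, days of admission are reviewed, and the list joins its last item with *and*. Consent cannot sensibly be an alternative to delirium. The article condenses a protocol (version 1.0) that is not shown, so the wording used at the site may be sound. Eligibility also precedes randomization and applies equally to both arms, so neither the allocation nor the type I error is touched. All of this stands. It limits the consequence, but the published rule is still wrong as worded and at odds with the screening text.

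A reader might go further and infer that patients not at risk of PICS are being enrolled. The document does not support that. The Introduction calls patients with COVID-19 especially susceptible to PICS, and the screening frame is ICU admissions. No section says that a survivor without the four markers is free of risk, that any such patient was enrolled, or how many exist. The Discussion does name delirium as a risk factor, which ties one of the four criteria to risk, but that does not make its absence mean no risk.

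A reader might also take the power figures as an expected loss. They are not. Zero benefit in the share q is an extreme case: the whole intervention arm receives PICS education, pain education depends on reported pain, and psychological treatment depends on the HAD depression score. None of these depends on the four markers. The figures are kept on the plan's own one-tailed basis, because the mismatch with the two-tailed analysis is a separate matter and should not be counted here.

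Finally, recruitment was anticipated to end on September 25, 2020, and the article appeared in July 2021. If that timetable held, a change of wording alters no enrolment. The clarification and the sensitivity analysis keep their value.

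**Conclusion.** The point holds as a defect of the stated rule. By its wording and the trial's own exclusions, the four ICU-severity criteria have no effect, and ICU-admitted COVID-19 survivors with none of the listed markers are eligible. This is certain from the text and needs no assumption beyond reading it literally. It contradicts the stated use of days of admission in screening and leaves the trial population unclear.

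Dilution of the at-risk population is possible but not shown. The fall from 80% to about 72%, 63% or 54% power rests on three assumptions: an SD of about 18.3 solved from the plan's own sample size, an assumed share of 10%, 20% or 30%, and no benefit at all in that share. The conclusion does not depend on these figures.

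**What to change.** Reconcile Study population with Methods of randomization and bias minimization by stating which criteria are mandatory and which are alternatives. The reading that makes every criterion operative and best fits the text is confirmed infection **and** signed consent **and** at least one of criteria (2) to (5). The document does not settle this, so the sponsor should confirm which rule was intended and which was applied at screening.

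Flag each enrolled patient who meets none of criteria (2) to (5), and report the number by arm. Keep the intention-to-treat analysis of all randomized patients as primary, and add a sensitivity analysis of the 6-month primary outcome without the flagged patients. The flag uses only characteristics fixed before randomization, so the arms remain comparable within the reduced set.

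The cost is a wording clarification and one extra analysis. APACHE II, ICU length of stay, ICU-acquired weakness and delirium are already collected at baseline (Outcome measurements), so no new data are needed. If enrolment is still open and patients without the markers were being accepted, recruitment could slow slightly. If it has closed, that cost does not arise.
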